### Data collection

After enrollment, participants undergo anthropometric measurements, including measurements of weight, height, waist circumference, and hip circumference, with the average of 3 measurements being used as the final values. The blood glucose concentrations during the 3 periods will be monitored through a continuous glucose monitoring (CGM) system (Sibionics Technology Co, Ltd) every 5 min. A designated study personnel member who is not involved in the data analysis will be responsible for monitoring and extracting data from the CGM terminal platform (Sibionics Technology Co, Ltd), removing all information capable of identifying participants before forwarding data to statistical analysis to ensure anonymity.

### Outcomes

The primary outcome is the postprandial blood glucose peak (PBGP) within 3 h after the first bite of the test diet. The secondary outcome is the postprandial 3-h glucose incremental AUC (iAUC_3h_), calculated by assessing the change in blood glucose concentrations from the fasting state (measured 30 min before test diet consumption) over the 3-h period following the intake of the test diet.

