### Randomization

The randomization process for the trial will be conducted by a statistician who is not involved in the data analysis to ensure impartiality. Allocation concealment will be achieved using sequentially numbered, opaque, sealed envelopes. The test diets will be designed in alphabetical letters. A random sequence will be generated using R software (R Foundation), with each participant’s order being independently randomized for each period. The order will be provided directly to the food preparation staff, who have no involvement in data collection and analysis. This study strictly implemented analyst blinding. Specifically, the statisticians responsible for data analysis remained completely unaware of which specific staple foods the letter codes represented until the final analysis was completed, and the results were locked.

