#### Individual-level N-of-1 trial analysis

To assess the PPGR to various staple foods at an individual level, Bayesian model will be performed. It is presupposed that individual observations of PBGP and iAUC_3h_ adhere to a normal distribution centered on each participant’s true average effect. The MCMC method will be used to estimate the posterior distribution of the parameters of interest. We will initiate 4 chains, with each executing 4000 iterations, culminating in a total of 16,000 sampling iterations. The Bayesian inference will be executed using the following equation for PBGP:(1)$${\text{PBGP}}_{i}=\beta_{0}+\sum_{j}\beta_{j}\cdot {\text{staple}\;\text{food}}_{j}+\epsilon_{i}$$in which the PBGP for participant *i* is modeled as the intercept, with the effect of each staple food *j* denoted as the intervention effect, and the random error for individual *i* modeled as a normal distribution with a mean of 0 and a large SD. Noninformative prior distributions will be incorporated into the model due to uncertainty regarding prior knowledge. Following the estimation of the posterior distribution of the effect of each staple food within the Bayesian model, the average value of the posterior distribution for differences between foods will be calculated, alongside the SE and 95% credible intervals. Standard procedures for warm-up periods, diagnostics for model convergence and stability, and residual checks will be applied. During the warm-up period, initial samples will be discarded to allow the chain to converge to a stationary distribution. The Gelman-Rubin test will be used to assess the convergence of the MCMC chains, with an *R*-hat value of <1.05, indicating that the chain has converged. The threshold for posterior probabilities will be set at 80% [28].

For a comprehensive evaluation of the PPGR of various staple foods among patients with diabetes, a weighted average response probability will be generated for each staple food. Using Bayesian models and sequentially using each staple food as a reference, we will estimate the posterior probability that the average difference between the reference food and the other 4 staple foods exceeds the MCID. As mentioned earlier, in this study, we define the MCID for PBGP as 0.78 mmol/L, and the MCID of iAUC_3h_ is 106.78 mmol/L·min, representing 10% of the difference between patients with T2DM and those with impaired fasting glucose, a difference that amounts to 1067.85 mmol/L·min [29].

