#### Population-level N-of-1 trial analysis

For the population-level assessment of the PPGR to different staple foods, a Bayesian generalized linear mixed regression model will be used to aggregate the results from multiple *N*-of-1 trials at the population level, incorporating both between-individual and within-individual variations. Individual regression models will be linked using a random-effects model, assuming that the individual-specific regression coefficients follow a normal distribution centered on the population’s average coefficient. Noninformative priors will be used to define the variance distribution of the parameters, ensuring the robustness of the analysis. The threshold for posterior probabilities will be set at 80%. Additionally, the posterior probability of the mean differences exceeding the MCID will be evaluated.

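### The primary peak-glucose models leave out the same-morning pre-meal glucose the trial already records, which costs precision, mainly in the individual food contrasts

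*Protocol article*

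**What the plan says.** **Outcome.** Protocol article, Outcomes: "The primary outcome is the postprandial blood glucose peak (PBGP) within 3 h after the first bite of the test diet". No baseline is subtracted. The secondary outcome, iAUC over 3 h, is calculated as a change "from the fasting state (measured 30 min before test diet consumption) over the 3-h period following the intake of the test diet". Under Data collection, glucose "will be monitored through a continuous glucose monitoring (CGM) system (Sibionics Technology Co, Ltd) every 5 min". A pre-meal value from the same device is therefore available on every test morning.

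**Models.** Individual-level N-of-1 trial analysis prints Equation 1 in full: an intercept, a sum of staple-food terms "with the effect of each staple food *j* denoted as the intervention effect", and a normal error. Population-level N-of-1 trial analysis says "Individual regression models will be linked using a random-effects model" and names no pre-meal covariate.

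**Design.** Randomization sets the diet sequence "with each participant’s order being independently randomized for each period". Study procedures gives five test days per period with a 3-day washout between tests, a provided dinner and a 12-h fast. The Discussion says that sensors are replaced every 12 days, and relies on replication and on random effects to deal with drift and CGM error.

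**The concern.** A peak that is not corrected for its starting level carries that morning's fasting glucose and any offset of the sensor then in use. With food terms only in the model, both go into the error term, although a measurement that could remove part of them is already collected.

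This matters most for the individual results. Each food is eaten on three mornings per person. The individual posterior probabilities of exceeding 0.78 mmol/L are built from those mornings, the WGRS is built from the probabilities, and the Discussion says that personal dietary recommendations will follow from the WGRS. Avoidable residual noise reduces the ability to tell one person's foods apart.

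Because Equation 1 is printed in full, this is a stated modelling choice and not a detail left to an unseen analysis plan.

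**Working it through.** **Inputs from the protocol**
- Sample size estimation: within-individual SD 1.2, between-individual SD 2.5, white rice v pasta difference 2.4, MCID 0.78 (all mmol/L); 3 cycles, 5 foods; N = 14.
- Decision rule: posterior probability of exceeding the MCID above 80%.
- Study procedures and Discussion: 3-day washout, 12-day sensors.

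**Assumed, because the documents give no value**
- r, the within-person correlation between pre-meal glucose and peak; or equivalently
- s_f, the day-to-day SD of pre-meal glucose including sensor offset. If it carries one-for-one into the peak, r = s_f/1.2.

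**1. The plan's own power figure.** The plan states 86.0% power and 2.0% type I error. A normal/t approximation with flat priors gives 91.7–92.2% and 2.5–2.8% if 2.5 is the SD of the individual food difference. It gives 78–79% and 4.8–5.2% if 2.5 is a per-food SD, and 87.2–87.8% and 3.3–3.6% with one cycle only. No reading gives both stated figures. That does not show an error, since the priors, variance structure and number of runs are not printed. The point here does not depend on it.

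**2. Precision of one person's two-food contrast, unadjusted.** SE = 1.2 × √(2/3) = 0.98, which is larger than the MCID of 0.78.

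**3. The same contrast, adjusted**
- Shared slope, well estimated: SE = 0.98 × √(1 − r²).
- Separate slope per person: 15 observations less 5 food means leave 10 residual df, so estimating the slope multiplies the contrast variance by about 1 + 1/8 = 1.125, and SE = 0.98 × √(1.125 × (1 − r²)).

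| assumed r | shared slope | separate slope |
|---|---|---|
| 0.3 | 0.93 | 0.99 |
| 0.5 | 0.85 | 0.90 |
| 0.7 | 0.70 | 0.74 |

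A separate slope breaks even when 1.125 × (1 − r²) = 1, that is r² = 0.111 and r = 0.33. Below that it loses precision.

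**4. Chance imbalance and false flags for one person.** The SD of the imbalance between two foods is s_f × √(2/3). The last three columns are the simulated chance of at least one false flag among a participant's 20 directed food pairs when no foods differ, a flag being a posterior probability above 80% of exceeding 0.78. The shared-slope column treats the slope as known.

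| assumed s_f (r) | imbalance SD | pairs with imbalance > 0.78 | unadjusted | shared slope | separate slope |
|---|---|---|---|---|---|
| 0.3 (0.25) | 0.24 | 0.1% | 47% | 45% | 47% |
| 0.5 (0.42) | 0.41 | 5.6% | 47% | 42% | 45% |
| 0.7 (0.58) | 0.57 | 17% | 47% | 36% | 38% |
| 0.9 (0.75) | 0.73 | 29% | 47% | 25% | 28% |

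The imbalance is part of the 0.98 and does not add to it. At s_f = 0.7, 0.49 × 2/3 = 0.33 and (1.44 − 0.49) × 2/3 = 0.63, which sum to 0.96 = 0.98².

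**5. Population level (2.5 read as the SD of the individual difference).** The contrast variance per person is 2.5² + 2 × 1.2²/3 = 7.21. At r = 0.5 it is 6.25 + 0.96 × 0.75 = 6.97. With N = 14, over s_f from 0.3 to 0.9, approximate power rises from 92.2% to between 92.3% and 93.4%, at most about 1.2 points.

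**6. Sensor coverage.** Even if the washout means a test on every third day, five tests span 1 + 4 × 3 = 13 days, longer than one 12-day sensor. Foods within a period are therefore compared across sensors.

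**The case against.** **The contrasts are unbiased.** A reader might infer that fasting shifts are systematically read as food effects. The documents do not support that. Order is randomised independently per participant and period, so pre-meal level is independent of food. It enters the residual and widens the credible intervals, and the exceedance probabilities reflect that. This part of the objection stands in full.

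**The noise is already counted.** The 1.2 is given as the within-individual SD for the peak, so on its face it includes fasting variation, and the sample size was simulated with it. This also stands: chance imbalance must not be added on top of the 0.98.

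**The gain may be small or negative.** It is tempting to say that r = 0.5 is worth an extra cycle, since 3/(1 − 0.25) = 4 observations per food. With a slope estimated per person it is 3/(0.75 × 1.125) = 3.56, and below r of about 0.33 there is a loss. This stands against a separate slope. It does not stand against a shared one, where the slope is estimated from all participants.

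**The plan has other safeguards.** The provided dinner, the fast, and the activity and alcohol limits steady the pre-meal state, and iAUC is already baseline-corrected. They reduce the variation without removing it, and the WGRS equation is defined on the peak. Replication balances sensor drift in expectation, not within one person's three mornings per food. A person-level random effect cannot remove a day or sensor shift within that person.

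**An absolute peak is coherent.** The MCID is defined on that scale. Agreed, which is why a covariate is preferable to switching the outcome to an increment.

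**Conclusion.** The point holds as a loss of precision, not as bias. The primary-outcome models omit a pre-meal measurement that the trial already collects, and the cost falls mainly on the individual contrasts that feed the WGRS and the personal recommendations. With a shared slope, the SE of 0.98 would fall to about 0.93 at r = 0.3, 0.85 at r = 0.5 and 0.70 at r = 0.7. The population-level conclusion would barely change.

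The size rests on an assumed r, a linear relation between pre-meal glucose and peak, and the protocol's 1.2 as the within-person SD of the peak. If r is low, little is gained. The change is worth making because it is cheap, but the planned analysis is valid without it.

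**What to change.** - Add same-morning pre-meal CGM glucose (for example, the mean of the readings before the first bite), centred within participant, as a covariate for PBGP in the hierarchical model, with one slope shared across participants.
- Take the individual food contrasts, the probabilities of exceeding 0.78 mmol/L and the WGRS from that adjusted model, or carry the shared slope into Equation 1. Do not estimate a separate slope for each participant.
- Keep the unadjusted PBGP analysis as a sensitivity analysis.
- Leave the MCID as it is. Covariate adjustment keeps the peak scale, whereas a peak increment would need its own justification.

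**Cost:** no new data, one extra parameter and a few lines of analysis text. The downsides are the assumption of a common linear slope and little gain if r turns out low.

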**FIGURE 1 fig1:**

Flowchart of *N*-of-1 trials for personalized differences in staple foods with diabetes. (Except that the 5 test diets are administered in an independently generated randomized sequence within each period, the other study procedures across the 3 periods, such as continuous glucose monitoring, safety evaluation, duration of the washout period, and provision of balanced dinners, are identical.) CGM, continuous glucose monitoring.

On the test day, participants will be required to rest for ≥10 min prior to the serving of the test diet. The test meal will be prepared and served at the Beijing Institute of Nutritional Resources restaurant across all participants. The cooking of each staple food follows strictly standardized preset procedures, using a fixed staple-to-water ratio and cooking time. For white rice, brown rice, and germ rice, the ratio of staple food (grams) to water (milliliters) is 1:1.25, and they will be cooked for 40 min using a Supor SY-60YC8001Q rice cooker (Zhejiang Supor Co, Ltd.). For rice noodles and pasta, the mass-to-volume ratio of staple food (grams) to water (milliliters) will be set to 1:10 to ensure that the rice noodles or pasta ensure complete submersion and uniform heating throughout the cooking process. They will be boiled for 10 min, after which the excess water will be drained thoroughly before being incorporated in the test diet. The time of the first bite will be synchronized with the glucose monitor intervals and recorded for each participant. The participants will be directed to refrain from consuming any additional food or to avoid engaging in strenuous physical activity for ≥3 h following the consumption of the test diet.

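### The iAUC_3h baseline is set 30 min before the meal, not over a window of CGM readings ending at the first bite, which costs precision in the secondary outcome

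*Protocol article*

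**What the plan says.** The Outcomes section of the protocol article names iAUC_3h as the secondary outcome. The increment is "the change in blood glucose concentrations from the fasting state (measured 30 min before test diet consumption" and is taken "over the 3-h period following the intake of the test diet". The section names one time for the reference. It does not say how many readings form it.

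Three other statements bear on this:

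- Data collection: glucose "will be monitored through a continuous glucose monitoring (CGM) system (Sibionics Technology Co, Ltd) every 5 min".
- Test-day procedures (text after Figure 1): "The time of the first bite will be synchronized with the glucose monitor intervals and recorded for each participant". The same text says that "participants will be required to rest for ≥10 min prior to the serving of the test diet".
- Individual-level N-of-1 trial analysis: "the MCID of iAUC_3h_ is 106.78 mmol/L·min, representing 10% of the difference between patients with T2DM and those with impaired fasting glucose". The section puts the underlying group difference at 1067.85 mmol/L·min, and its posterior-probability threshold is 80%.

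Each participant eats each food once in each of three periods (Study procedures), so an individual food contrast rests on three meals against three.

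**The concern.** The area starts at the first bite, but its zero level is set half an hour earlier. Any error in that level is subtracted from every later reading and so accumulates over the whole 3 h. Two sources matter: short-term sensor noise at the reference time, and real glucose change between -30 min and the first bite, which is then counted as response to the food. The design already records readings closer to the meal, including one at or near time zero, and the definition does not use them.

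What is at stake is the precision of iAUC_3h and of the probabilities that food differences exceed its MCID. Individual-level results are the most exposed, since three meals per food leave little averaging.

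**Working it through.** **Inputs from the article.** Integration window 180 min; CGM interval 5 min; iAUC MCID 106.78 mmol/L·min; three meals per food per person. **Inputs not in the article, assumed here.** SD s of the baseline reading around the true level at the first bite, 0.3 to 0.5 mmol/L (wider range 0.2 to 0.8); lag-1 (5-min) autocorrelation of errors, 0 to 0.9.

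**1. The article's own figure.** 0.10 × 1067.85 = 106.785, stated as 106.78. It reproduces.

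**2. Readings available.** From -30 to 0 min in 5-min steps, both ends included: 30/5 + 1 = 7.

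**3. Effect of a baseline error.** An error e shifts the net area by -180 × e. The error that moves one meal by a full MCID is 106.78/180 = 0.593 mmol/L.

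**4. Noise per meal and per contrast.** Per meal the SD is 180 × s. For two foods with three meals each it is 180 × s × sqrt(2/3).

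| s (mmol/L, assumed) | per meal | % of MCID | 3-vs-3 contrast |
|---|---|---|---|
| 0.2 | 36 | 34% | 29 |
| 0.3 | 54 | 51% | 44 |
| 0.5 | 90 | 84% | 73 |
| 0.8 | 144 | 135% | 118 |

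**5. Net or positive-only area.** A simulation on an assumed curve (fasting 8 mmol/L, peak 5 mmol/L above it, s = 0.5, independent errors in all readings) gave a total error SD of 90.8 for net area and 90.0 for area above baseline only. The 180-min multiplier therefore holds almost unchanged while glucose stays above baseline.

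**6. Gain from the seven-reading mean.** The SD ratio to one reading is sqrt(sum of the 7 × 7 AR(1) correlation matrix / 49).

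| lag-1 autocorrelation | ratio | reduction | baseline part at s = 0.3 | at s = 0.5 |
|---|---|---|---|---|
| 0 | 0.378 | 62% | 54 → 20 | 90 → 34 |
| 0.7 | 0.720 | 28% | 54 → 39 | 90 → 65 |
| 0.9 | 0.893 | 11% | 54 → 48 | 90 → 80 |

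When the errors of the post-meal readings are included (same simulation, s = 0.5, net area), the total error SD falls from 90.8 to 36.6, from 95.9 to 69.2 and from 95.7 to 81.1 for the three autocorrelations.

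**7. Drift.** Suppose glucose changes linearly by 0.3 mmol/L from -30 min to the first bite (assumed). A -30 min baseline shifts the area by 180 × 0.3 = 54. The -30 to 0 mean sits on average 15 min before the bite, so the shift is 180 × 0.15 = 27. A -10 to 0 mean sits on average 5 min before, so the shift is 180 × 0.05 = 9.

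**8. Trade-off for a short window.** A -10 to 0 mean has three readings. The SD ratio is sqrt((3 + 4r + 2r²)/9): 0.577 at r = 0, sqrt(6.78/9) = 0.868 at r = 0.7, and sqrt(8.22/9) = 0.956 at r = 0.9. It removes less noise than seven readings but more drift.

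**The case against.** **The text never says that one reading is used.** This is correct. A reader might infer a single value, and that is the natural sense of the wording, but a short averaging window is not excluded, and a condensed article may leave the number of readings to a fuller document. What remains is that the time itself is stated, and it is the one furthest from the meal. If a window is meant, the sentence needs to say so.

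**The baseline need not precede the rest.** A reader might infer that the -30 min point comes before the participant has settled. The rest requirement is a minimum of 10 min, so rest may already have begun by then. The documents show no contradiction here.

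**There is no bias.** A reader might infer that foods are compared unfairly. A constant sensor offset cancels in the increment, the same rule applies to every food, and order is randomised independently in each period. The error therefore adds within-person noise and does not favour a food. This stands in full.

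**The size is assumed.** Also correct. The article gives neither the reading SD nor its autocorrelation, and participants have fasted for 12 h, so drift may be small. The MCID is also a decision threshold; it does not measure total variability. If the within-individual SD of 1.2 mmol/L given for PBGP under Sample size estimation is borrowed as the SD of the mean increment, total iAUC SD is 180 × 1.2 = 216. Cutting the baseline part from 54 to 39 then gives sqrt(216² - 54² + 39²) = 213, a gain of about 1.5%. Cutting it from 90 to 65 gives 207, about 4%. A smaller total SD would make the gain larger. This argues for modest priority. It does not argue for keeping the less precise definition, since the window mean did better in every case examined.

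**Conclusion.** The point holds as a matter of precision in a secondary outcome. The article fixes the iAUC_3h reference at -30 min although better-placed readings are already collected, and an error in that reference is carried at up to 180 min. The multiplier, the seven readings and the 0.593 mmol/L equivalence follow from the article's own figures. The 54 to 90 mmol/L·min per meal, and the reductions of 11% to 62%, rest on assumed SDs and autocorrelations.

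The consequence is added noise in iAUC_3h and in the probabilities that differences exceed its MCID, mostly at the individual level. PBGP is defined without a baseline, and the sample size rests on PBGP, so neither is affected. This is a free improvement of minor priority.

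**What to change.** In the Outcomes section, define the iAUC_3h baseline as the mean of the CGM readings over a fixed window ending at the first bite, and state the window. Two reasonable choices are -30 to 0 min (seven readings, most noise reduction) or -10 to 0 min (three readings, least drift, and within the guaranteed rest). A -15 to 0 min window would begin before the 10 min that are guaranteed if eating starts at serving. State also whether area below baseline is counted.

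Optionally, and as a separate gain in precision, the same pre-meal mean could enter the PBGP model as a covariate. That would change the primary model and should be decided on its own merits.

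The cost is one or two sentences, settled before the data are analysed. No new measurements, visits or participants are needed.
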